## Abstract

**Background:**

Breast cancer survival rates are significantly lower among African-American women compared to white women. In addition, African-American women with breast cancer are more likely than white women to die from co-morbid conditions. Obesity is common among African-American women, and it contributes to breast cancer progression and the development and exacerbation of many weight-related conditions. Intervening upon obesity may decrease breast cancer and all-cause mortality among African-American breast cancer survivors.

**Methods/Design:**

Moving Forward is a weight loss intervention being evaluated in a randomized trial with a projected sample of 240 African American breast cancer survivors. Outcomes include body mass index, body composition, waist:hip ratio, and behavioral, psychosocial and physiological measures. Survivors are randomized to either a 6-month guided weight loss intervention that involves twice weekly classes and text messaging or a self-guided weight loss intervention based on the same materials offered in the guided program. The guided intervention is being conducted in partnership with the Chicago Park District at park facilities in predominantly African-American neighborhoods in Chicago. Recruitment strategies include direct contact to women identified in hospital cancer registries, as well as community-based efforts. Data collection occurs at baseline, post-intervention (6 months) and at a 12-month follow-up.

**Discussion:**

This study evaluates a community-based, guided lifestyle intervention designed to improve the health of African-American breast cancer survivors. Few studies have addressed behavioral interventions in this high-risk population. If successful, the intervention may help reduce the risk for breast cancer recurrence, secondary cancers, and co-morbid conditions, as well as improve quality of life.

**Trial registration:**

U.S. Clinicaltrials.gov number: NCT02482506, April 2015

## Background

Breast cancer is the second leading cause of cancer death among African-American women [1]. Despite lower incidence, breast cancer mortality rates for black women are higher than those for women of other racial/ethnic groups even after controlling for age, socioeconomic status, tumor stage and histology, hormone receptor status, and menopausal status ([2, 3], http://www.seer.cancer.gov/). Ninety- two percent of white women will survive for at least five years after diagnosis, compared to only 77 % of black women [4]. Additionally, African-American women with breast cancer are more likely to die from co-morbid conditions, including diabetes and hypertension [5, 6]. These disparities are not easily explained and involve multiple issues related to social determinants of health [7]. However, obesity and behavioral factors are likely additional and related contributors.

Obesity contributes to breast cancer progression, as well as the development and exacerbation of many co-morbid conditions [8–13]. This relationship remains after adjusting for stage at diagnosis, nodal status, treatment type, and menopausal status prior to diagnosis [8, 14–16]. Obesity is hypothesized to promote tumor progression by (1) producing higher concentrations of estrogen and testosterone [2, 17, 18], (2) contributing to insulin resistance, leading to increased levels of insulin-like growth factor-I (IGF-1) and insulin-like growth factor-binding protein-3 (IGFBP-3) [10, 19, 20], and (3) contributing to chronic inflammation [21]. This paper describes the study protocol for Moving Forward: A weight loss program for African-American breast cancer survivors.

Eighty-two percent of African-American women are overweight or obese [22] and many have dietary and physical activity patterns that contribute to obesity, cancer and other health risks [11, 23–26]. Among breast cancer survivors, baseline dietary data from the Women’s Healthy Eating and Living Study showed that African-American survivors (*N* = 118) consumed significantly more calories from fat and less fruit than Asians or whites, and they were less likely than other women to meet guidelines for physical activity [27]. Findings from a survey of 468 African-American breast cancer survivors documented that most did not exercise regularly, and median television viewing was over 5 h daily [28]. The combined effects of obesity, unhealthy diet and inactivity may contribute to the disparity in breast cancer survival among African-American women and may be the easiest modifiable factors to address in the near term [12, 29].

Several weight loss interventions report beneficial results for breast cancer survivors, including weight loss [30–34], prevention of weight gain [35], improved body composition and lipids [33, 36], decreases in sex hormones [36], decreases in dietary fat intake [35], increases in fruit, vegetable and/or fiber intake [35], increased physical activity [30, 35] and improved psychological status [35]. Inclusion of African-American women in these trials was limited. Considering the high rates of breast cancer and all-cause mortality, co-morbidities, and obesity, weight loss is an important goal. However, due to a complex interaction of behavioral, cultural and societal factors, African-American women are less likely to participate in traditional weight loss programs, more apt to drop out, and lose less weight than white women [37, 38].

Recent efforts support the feasibility of weight loss interventions for African-American breast cancer survivors [31, 39, 40] However, studies were not fully powered and none examined the physiological impact of weight loss for African-American breast cancer survivors. Weight loss trials with white breast cancer survivors support the positive impact of weight loss on intermediate markers of breast cancer including sex hormones (estrogen, estradiol, testosterone, sex hormone binding globulin), chronic inflammation (C-reactive protein [CRP], interleukin-6 [IL-6], and TNF-α), and hyperinsulinemia (nsulin-like growth factor-1 [IGF-1], insulin-like growth binding protein-3 [IGBP3]). These data, along with those for body composition (percent body fat vs lean mass), are particularly important for African-American survivors given the historically low levels of weight loss observed in interventions. Gathering body composition and biological data will enhance our understanding of how weight loss, even if minor amounts, may impact breast cancer recurrence risk and overall health risk among African-American women.

## Methods/Design

### Study design

Moving Forward is a randomized trial that examines the effects of a culturally tailored guided weight loss program as compared to a self-guided weight loss program on the BMI, body composition and waist:hip circumference of 240 overweight/obese African-American breast cancer survivors. Diet and physical activity patterns, intermediate markers of breast cancer recurrence (i.e., sex hormones, markers of chronic inflammation and hyperinsulinemia), fatigue and quality of life will also be examined.

The study is based in eight Chicago Park District facilities located within communities that are predominantly African-American. Figure 1 provides an overview of the study design. Figure 2 provides an overview of the conceptual framework for the study.

**Fig. 1 Fig1:**
[figure not shown]
Study Design

**Fig. 2 Fig2:**
[figure not shown]
Study Conceptual Framework. The independent variable is group assignment. It is expected that outcome results will be mediated by self efficacy at the individual level, social support at the interpersonal level and perceived access to healthy eating and exercise resources at the community level

### Ethics

The study procedures were reviewed and approved for ethical treatment of human subjects by the University of Illinois at Chicago Institutional Review/Ethics Board.

### Procedures

Women who respond to recruitment efforts complete a brief telephone interview to verify eligibility. Next, confirmation of stage I, II, or III breast cancer and approval for participation in a weight loss program that includes moderate physical activity is sought from the participant’s primary care physician (PCP) and/or oncologist. Once eligibility is established, participants are asked to come in for an interview and physical assessment. At the beginning of this appointment, staff meets individually with each participant to obtain written informed consent. They then complete a 75-min in person interview, a blood draw, blood pressure measurement, dual energy x-ray (DXA), and height and weight measurements. All participants are also asked to wear an accelerometer for 7 days during waking hours. Participants receive a $20 incentive for the interview, $10 for the blood draw, $10 for the DXA and $10 for wearing the accelerometer. Subsequently, participants are randomly assigned to one of two 6-month interventions: (1) Moving Forward guided weight loss intervention (MFG) or (2) Moving Forward self-guided weight loss intervention (SG). Participants once again complete the entire assessment process post-intervention and at a 12-month follow-up.

### Recruitment

Recruitment efforts include a number of different strategies. The most effective strategy relies on patient lists from cancer registries of three academic hospitals. Patients who were diagnosed with stages I, II, or III at least 6 months prior receive letters describing the study, followed by phone calls to assess interest and screen for eligibility. In addition, community-based efforts revolve around a number of community and institutional partners, including breast cancer support organizations, local churches, block clubs, community centers and community leaders. We also post notices within on-line communities that serve the African-American community.

### Eligibility

Inclusion criteria: (1) self-identify as Black or African-American (including individuals who are bi-racial but identify themselves as Black or African-American); (2) female; (3) Stage I, II, or III invasive breast carcinoma; (4) completed treatment (surgery, chemotherapy and/or radiation) at least six months *prior to* recruitment (ongoing treatment with adjuvant endocrine therapies is acceptable); (5) age 18 or above at time of diagnosis; (6) Body Mass Index (BMI) at least 25 kg/m^2^ – chosen because this includes only those participants who are overweight and would not be harmed by a 7 % weight loss; (7) physically able to participate in a moderate physical activity program as assessed by self-report and PCP/oncologist approval; (8) agree to random assignment and data collection; and (9) able to attend twice weekly classes for six months.

Exclusion criteria: (1) plans to move from the community during the study; (2) currently pregnant, less than 3 months post-partum, or pregnancy anticipated during the study; (3) taking weight loss medication prescribed by a doctor; (4) participation in another structured weight loss program that uses special foods; or (5) weight loss surgery in the past year, or planned weight loss surgery in the next year.

### Measures

#### Demographics

Demographic data include name, address, date of birth, marital status, number of children, education, occupational status, annual income, and insurance status.

#### Breast cancer treatment history

Diagnosis and treatment history (e.g., chemotherapy, radiation, previous and current adjuvant endocrine therapies) are collected from the treating oncologist and will be used for descriptive purposes only.

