#### Biological/physiological outcomes

##### Biomarkers of breast cancer recurrence risk

A fasting blood sample is drawn according to standard procedures by a clinical research center phlebotomist. We chose markers for three proposed mechanisms by which obesity may contribute to breast cancer progression: altering levels of sex hormones (markers: estradiol, estrogen, sex hormone-binding globulin, testosterone), hyperinsulinemia (markers: IGF-I, IGBP3, C-peptide), and chronic inflammation (marker: C-reactive protein, IL-6) [58]. Staff at the clinical research center processes the blood samples according to standard procedures for storage. Briefly, a total of 30 ml of blood is collected in red top vacutainer tubes (without anticoagulant). Blood (approximately 15 ml) is allowed to clot for 20 min and subsequently centrifuged at 2500 rpm for 20 min to separate serum. Staff collects, aliquots serum, which is frozen at-80 °C until analysis. All breast cancer biomarkers are measured using commercially available ELISA kits (R&D Systems and Alpco). Each sample is assayed in duplicate and repeated if variability exceeds 15 %. We will monitor quality control of laboratory tests by ensuring internal positive and negative controls are within the parameters of the test kit for each assay and by evaluating for trends over time.

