### Statistical analyses

#### Power computations

Calculations were conducted for hierarchical longitudinal designs with differential attrition rates using software provided by Roy et al. [79] Results showed that an initial sample of 240 participants is sufficient to detect an effect size of 0.4, assuming attrition of about 10 % at each time point with power of 0.8 for a two -tailed test. Power will increase with the inter-correlation of observations over time, which we estimated conservatively at 0.4. The addition of covariates to the model will also increase power.

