#### Data analysis

For a two-group randomized trial with repeated measures the mixed (multilevel) model is the preferred mode of data analysis [80]. With only two time points, the analysis reduces to a test of the difference between treatment groups in gains or losses in the outcome variable between baseline and 6-month follow up. The model easily generalizes to three time points (including the 12-month visit), in which case time can be indexed in simple linear fashion or represented either in quadratic form or via indicator variables for the first and second follow up measures. In that case, the analysis focuses on between group differences in outcome trajectories over time.

Our hypothesis is that subjects in the MFG condition will experience greater rates of weight loss, improved diet and physical activity patterns and other positive outcomes than subjects in the SG group. A major advantage of casting data analysis in the framework of the generalized linear (regression) model is that it easily accommodates covariates. One important covariate is time since diagnosis, which will be included in all analyses. A potentially important aspect of our modeling will be the investigation of dose–response effects. We will have data on frequency and pattern of attendance for each subject, which will allow us to model outcomes as a function of intensity of treatment.

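### The descriptive-only rule for diagnosis and treatment history sits in tension with the time-since-diagnosis covariate and bars a useful adjustment of the sex-hormone outcomes

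*Protocol article*

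**What the plan says.** Four statements in the protocol article bear on this.

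- *Breast cancer treatment history* defines the item as "Diagnosis and treatment history (e.g., chemotherapy, radiation, previous and current adjuvant endocrine therapies") and states that these data "are collected from the treating oncologist and will be used for descriptive purposes only".
- *Data analysis*: "One important covariate is time since diagnosis, which will be included in all analyses". No other covariate is named there.
- *Eligibility* requires surgery, chemotherapy and radiation to have ended at least six months earlier, but "ongoing treatment with adjuvant endocrine therapies is acceptable".
- *Biomarkers of breast cancer recurrence risk* gives the first of three mechanisms as "altering levels of sex hormones (markers: estradiol, estrogen, sex hormone-binding globulin, testosterone").

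In addition, *Power computations* says that adding covariates will increase power, and *Randomization* describes allocation by site without stratifying on therapy. No section exempts the hormone outcomes from the descriptive-only rule.

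**The concern.** There are two problems of different weight.

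The first is consistency. A covariate in every model is not a descriptive use, and time since diagnosis is diagnosis information. A reader of the measures section and a reader of the analysis section would come away with different rules.

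The second has more practical effect. Endocrine therapy, as its name says, is directed at the hormone system that four of the outcomes measure. The plan admits women taking it, records who they are, and then forbids using that record in analysis. This is a stated prohibition, not a detail left to a fuller document: an analysis plan that adjusted the hormone models for therapy would depart from the published protocol. Differences between users and non-users then stay in the residual variance of the hormone models, and an uneven split of users between arms cannot be corrected within the stated plan. The Discussion presents the biological markers as a distinctive feature of the trial, so their analysis deserves this care.

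**Working it through.** **Step 1. The texts side by side.** The restriction covers diagnosis as well as treatment, and names current endocrine therapy. The covariate rule uses time since diagnosis in all analyses. *Data analysis* does not say where the diagnosis date comes from. Other sources are possible: *Recruitment* describes registry lists that select on time since diagnosis, though these cover only registry recruits, and *Eligibility* requires age 18 or above at diagnosis, with eligibility checked by telephone interview (*Procedures*). So the diagnosis part is a tension in the wording, not a strict impossibility. For endocrine therapy there is no competing statement; the prohibition simply stands.

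**Step 2. Reproduce the stated power.** *Power computations* says that "an initial sample of 240 participants is sufficient to detect an effect size of 0.4". The other inputs given there are a loss of roughly a tenth of the women per visit, a power of 0.8 and two-sided testing. Two-sided alpha 0.05 and 1:1 allocation are my assumptions, as the section states neither.

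- Per arm: n = 2 × (1.960 + 0.842)² / 0.4² = 98.1, so 99, or 198 in total.
- With 10 % lost at each of two follow-ups, 0.9 × 0.9 = 0.81 remain: 198 / 0.81 = 244.4, so 245, against 240 stated.
- Power = Φ(0.4 / √(2/n) − 1.960). At 12 months n = 120 × 0.81 = 97.2 per arm and power is 0.796. At 6 months n = 120 × 0.90 = 108 per arm and power is 0.836.

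The stated 0.8 is reproduced on this reading. Stricter readings, with the effect scaled to the raw SD, give 0.75 to 0.78 (three-visit mixed model, correlation 0.4) or 0.72 to 0.77 (change score). The point does not depend on the choice.

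**Step 3. What adjustment could add.** Let R² be the share of residual hormone variance explained by baseline therapy. The documents give no value, so a range is shown. The residual SD falls from 1 to √(1 − R²), and power becomes Φ(0.4 / (√(1 − R²) × √(2/n)) − 1.960).

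| R² (assumed) | Power, 6 months (108 per arm) | Power, 12 months (97.2 per arm) |
|---|---|---|
| 0 | 0.836 | 0.796 |
| 0.05 | 0.854 | 0.816 |
| 0.10 | 0.873 | 0.836 |
| 0.20 | 0.908 | 0.877 |
| 0.30 | 0.940 | 0.915 |

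The gain at 6 months runs from 0.854 − 0.836 = 0.018 to 0.940 − 0.836 = 0.104. At 12 months it runs from 0.816 − 0.796 = 0.020 to 0.915 − 0.796 = 0.119.

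**Step 4. Chance imbalance.** With 120 per arm and a share p of users, the SD of the between-arm difference in user share is √(2p(1 − p)/120): 0.059 at p = 0.3, 0.065 at p = 0.5 and 0.063 at p = 0.6 (p assumed). To scale this, suppose users and non-users differ by D residual SDs, so that R² = p(1 − p)D². At p = 0.5, R² = 0.05 gives D = √(0.05/0.25) = 0.447 and R² = 0.30 gives D = √(0.30/0.25) = 1.095. A one-SD imbalance then moves the arm difference by 0.0645 × 0.447 = 0.029 to 0.0645 × 1.095 = 0.071 SD, beside a design effect of 0.4. This is the loss in Step 3 seen in a single trial, not a further loss.

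**The case against.** The strongest defence has three parts.

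*The diagnosis clash is loose drafting.* The covariate rule is specific and says it applies to all analyses, and a diagnosis date can be had outside the restricted item. This largely stands, and is why the point is put as a tension. A clarifying clause is still needed, because no source for the date is named.

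*Randomisation already protects the comparison.* This stands. Omitting a baseline variable does not bias the arm contrast, and a repeated-measures model that contains the baseline value absorbs part of any stable drug effect. That makes the lower values of R² more plausible than the higher ones. It does not cover women who start, stop or switch therapy during follow-up, whose changes remain as noise.

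*The affected outcomes are not the leading ones.* *Study design* puts BMI, body composition and waist:hip first and lists the markers as also examined. This stands and limits the weight of the point.

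A reader might infer more: that women on therapy cannot respond, that the pooled hormone effect is therefore badly diluted, that a null result would mean nothing, and that the main hormone estimate should come from non-users. The documents do not support this. They say nothing about users' response, and they do not tie the 0.4 effect to any hormone. The case for restriction depends on near-zero response in every user. If users kept half the response, then at 20 / 30 / 40 / 50 % use the pooled 6-month power (108 per arm, baseline-adjusted with correlation 0.4) would be 0.82 / 0.78 / 0.72 / 0.67, above the 0.81 / 0.76 / 0.69 / 0.61 in non-users alone. Restriction would also change the question in a trial that chose to enrol users. A pooled null would still be a valid, if less precise, estimate of the average effect in that population.

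**Conclusion.** The point holds in a limited form. The descriptive-only rule is in tension with the covariate rule, and it needlessly bars adjustment of the sex-hormone and SHBG outcomes for a variable already in hand. The arm comparison is not biased and the weight conclusions are untouched. What is lost is precision, protection against chance imbalance, and some ease in interpreting the hormone results.

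The size is about 2 to 10 points of power at 6 months and 2 to 12 at 12 months. This rests on an assumed R² of 0.05 to 0.30, a 0.4 SD effect borrowed from the general power statement, two-sided alpha 0.05 and equal allocation. If therapy explains almost nothing beyond the baseline value, the gain is close to nil. The wording conflict does not depend on any of these assumptions.

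**What to change.** In *Breast cancer treatment history*, replace the descriptive-only restriction with wording that permits two analytic uses:

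1. Diagnosis date feeds the time-since-diagnosis covariate, with its source named.
2. Baseline endocrine therapy (class or none) enters the models for estradiol, estrogen, testosterone and SHBG as a prespecified covariate.

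Keep the full randomised sample as the main hormone estimate. Report an arm-by-therapy term and the effects within therapy strata as secondary. Where a change in therapy between visits is known, add a sensitivity analysis for it.

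The cost is a few sentences. Baseline therapy is already collected, the sample of 240 is unchanged, and no clinical procedure is affected. The article does not say whether therapy is recorded again after baseline. If it is not, a brief update at the 6- and 12-month visits would make the sensitivity analysis more complete, but the main change does not depend on it.

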#### Co-morbid conditions

Respondents review a list of sixteen health problems (i.e., hypertension/high blood pressure, diabetes, arthritis) and report if they have ever been told by a doctor that they have this particular condition.

